### Participant selection and enrolment

Any patient (18–50 years) who requires a CS as part of their clinical care will be screened for inclusion. The potential participants will be identified using hospital clinical lists, where lists relate to a pre-booked CS a Good Clinical Practice (GCP) trained research midwife who is a member of the clinical care team will assess the eligibility of patients to participate in the study according to inclusion/exclusion criteria using screening form. The woman will then be provided with the participant information sheet at this meeting by the research midwife. In addition, if a pregnant woman is booked for CS at a meeting they may be informed about the study by a research midwife or their clinical care team and provided with a participant information sheet. The participants will receive information about the study well in advance (at prior clinic appointments) and at least 24 hours prior to CS so that all participants have sufficient time to consider taking part.

This study plans to compare data from obese (BMI ≥ 30 kg/m^2^) and non-obese women (BMI < 30 kg/m^2^) at the time of booking (10–14 weeks of pregnancy). At least 15 participants are required for each arm with a total of 30 participants. The study sequence is summarised in Table 2.

**Table 2 Tab2:** Summary of the C-LACE study sequence and methodology

Timing	Activity
Caesarean section booking clinic	Clinic list will be reviewed for eligible participants using the screening form
On the day of caesarean section	A Venflon cannula will be inserted into the woman as part of the research process to enable withdrawal of the required blood samples without the need for additional needles. This second access point will ensure that the blood sampling is minimally disruptive to the CS procedure.
At 30–40 days post-caesarean section	Participant’s medical file and notes will be reviewed by the research midwife to identify any post-surgical site infection which will be recorded on the 6-week outcome form. Research midwife will attempt to contact the participant 3 times between 30 and 40 days post-CS to complete the follow-up interview form.
Samples analysis	Blood and adipose tissue will be analysed by LC-MS/MS [15]

*GCP* Good Clinical Practice, *CS* Caesarean section, *LC-MS/MS* liquid Chromatography with tandem mass spectrometry

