### Data collection methods {18a}

Background information will be collected from each participant using the baseline form. This information is required for interpretation of the data and dissemination.

Following the collection of the data from all forms (screening, consent, baseline, eligibility reassessment, operation, discharge, follow-up interview, 6-week record check) will be filled, signed and shared via the secure system; this system can be accessed at the university and the hospital and ensures the security of data, any data, entered will be anonymised.

The study has two parts: part A, which is blood and adipose tissue sampling for cefuroxime concentrations; part B, is a follow-up of patients’ post-partum at between 30 and 40 days to record the incidence of post-surgical infection.

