#### Part B: Follow-up for post-surgical infection

At between 30 and 40 days post-CS, the study participants will be contacted by telephone by a research nurse/midwife from the research team and a review will be made to record any type of post-surgical infection. The follow-up interview form will be used to record the details of any infection reported. If the participant attended to the hospital for a post-natal appointment at 30–40 days, the interview can be conducted at that time to minimise the burden to the participant.

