#### Success criteria and assessment of C-LACE pilot and feasibility study

These criteria applied to participants consented and did not withdraw from the study at any time-point of C-LACE study:
Patients’ recruitment rate: as per Birmingham Women’s Hospital Caesarean Section rate, recruitment of 30 patients would be achievable easily within 3 months. If this was not achieved, the protocol (specific inclusion and exclusion criteria) would be reviewed and reassessed.Collecting samples: this pilot and feasibility study would be considered successful if plasma and adipose tissue samples at the time of incision and time of closure and plasma sample at time of recovery were successfully collected for ≥ 75% of participant in each arm. If this was not achievable, the sampling strategies will be revised and reassessed.Sample analysis: this pilot and feasibility study would be considered successful if ≥ 80% of plasma and adipose tissue samples collected were successfully analysed via the analytical method described; If not, sampling handling, transferring and sample analysis protocol will be revised and reassessed.Data collecting: this pilot and feasibility study would be considered successful if ≥ 80% of data collecting forms was fulfilled for each participant; if not, logistics and study procedure of C-LACE study will be revised at Birmingham Women’s Hospital.Follow-up: the described follow-up protocol will be considered successful if participants’ retention were ≥ 80%. The participant will be considered as lost to follow-up, if the participant could not be contacted and the patients file and notes were not reviewed.

Analysis and sub-analysis of outcomes and success criteria of C-LACE pilot and feasibility study will be made to explore the reasons of unsuccessful.

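### As worded, the form-completion criterion fails if a single woman is lost to follow-up, while the retention criterion in the same list tolerates up to six losses among 30

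*Protocol article*

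**What the plan says.** The relevant list is in the protocol article, section *Success criteria and assessment of C-LACE pilot and feasibility study*. It applies to women who consented and did not withdraw. Two of its items matter here.

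- **Data collection.** The pilot counts as successful on this item if at least "80% of data collecting forms was fulfilled for each participant". If not, logistics and study procedure at the hospital are to be revised.
- **Follow-up.** The article says "the described follow-up protocol will be considered successful if participants’ retention were ≥ 80" per cent. A woman is lost "if the participant could not be contacted and the patients file and notes were not reviewed". The section on missing data repeats this definition and adds that review of the notes alone counts as follow-up.

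*Data collection methods {18a}* names the forms: "screening, consent, baseline, eligibility reassessment, operation, discharge, follow-up interview, 6-week record check". That makes eight. Table 3 in *Study assessments {13}* shows the same eight, plus a column for collecting and labelling samples, and puts the interview form and the medical record check form at follow-up. On numbers, *Participant selection and enrolment* states: "At least 15 participants are required for each arm with a total of 30 participants".

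**The concern.** The sampling criterion in the same list is set as a share of participants in each arm (at least 75%). The forms criterion has no such share: read as written, every woman must reach 80%. Its result is therefore decided by the one participant with the fewest forms.

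The two follow-up forms are a quarter of the eight, so losing a woman to follow-up takes her below 80% however complete the rest of her record is. Any loss that the retention criterion accepts therefore breaches the forms criterion.

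The article makes assessment of process and procedure the main objective of the pilot, and data collection with form completion is a listed outcome. If the rule is followed as written, data collection that is good overall could be reported as unsuccessful and the study procedure revised because of one record. In the same report, follow-up would be declared a success.

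**Working it through.** The article derives no figure for this point, so there is none to reproduce. The check uses its own counts.

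**Inputs**
- Forms per participant: 8 (*Data collection methods {18a}*; Table 3).
- Forms due at follow-up: 2, the interview form and the record check form (Table 3).
- Forms threshold: 80% for each participant. Retention threshold: 80% of participants (both in the success criteria).
- Participants: 30, the planned total, assuming none withdraws.

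**Step 1: forms needed per woman.** 0.80 × 8 = 6.4, so at least 7 of 8. With 7/8 = 87.5% she passes; with 6/8 = 75.0% she fails.

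**Step 2: a woman lost to follow-up.** She was not contacted, so there is no interview form. Her notes were not reviewed, so there is no record check form. Her best case is (8 − 2)/8 = 75.0%, which fails. The result does not depend on how forms are counted:

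| Items counted | Best case if lost | At least 80%? |
|---|---|---|
| 9 (sample labelling added) | 7/9 = 77.8% | No |
| 8 (as listed) | 6/8 = 75.0% | No |
| 7 (screening form left out) | 5/7 = 71.4% | No |
| 6 (screening and consent forms left out) | 4/6 = 66.7% | No |

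**Step 3: losses that retention allows.** 0.80 × 30 = 24, so 30 − 24 = 6 losses.

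| Women lost | Retention | Retention criterion | Forms criterion as worded |
|---|---|---|---|
| 0 | 30/30 = 100% | Pass | Pass, if no woman lacks more than one form |
| 1 | 29/30 = 96.7% | Pass | Fail |
| 6 | 24/30 = 80.0% | Pass | Fail |
| 7 | 23/30 = 76.7% | Fail | Fail |

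The two criteria disagree for every number of losses from one to six.

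**Step 4: how often this might happen.** The documents give no loss rate, so the rates q below are assumptions, as is independence between women. The chance of at least one loss is 1 − (1 − q)^30.

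| Assumed loss rate q | Chance of at least one loss among 30 |
|---|---|
| 0.5% | 1 − 0.995^30 = 14% |
| 1% | 1 − 0.99^30 = 26% |
| 2% | 1 − 0.98^30 = 45% |
| 5% | 1 − 0.95^30 = 79% |

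At 2% and at 5% loss, the chance that retention passes (at least 24 of 30) is 99.9% or more.

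**The case against.** **The wording may be looser than it looks.** The sentence could mean that completion is assessed woman by woman, with nothing said about how women combine, or that an average is intended. A pooled or averaged reading would remove the conflict: six losses would give (24 × 8 + 6 × 6)/240 = 228/240 = 95%. But the text states neither reading, and the sampling criterion shows that the authors gave a participant share where they meant one. A threshold whose result reverses between readings needs rewording in any case.

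**Losses may be very rare.** This has force. Loss requires both failure to make contact, with three attempts planned, and no review of the notes. That review is done by hospital staff and does not need the woman to be reached. The article expects little missing data. A woman who is only unreachable by telephone has 7/8 and passes, provided that nothing else is missing. For this reason the range in Step 4 starts at 0.5%, and no single rate in it should be quoted as the expected one. Still, the article itself sets a retention threshold that accepts 20% loss, so the two criteria should be able to stand together.

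**Nothing irreversible follows.** This also stands. A reader might infer a stop/go rule that one missing record could trip. The documents do not support that: failure leads to revision of logistics and procedure, and the section promises to explore the reasons for any lack of success, so one lost woman would be identified as the cause. No concentration measurement or comparison between arms is affected.

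**The two criteria judge different things.** Form logistics and the follow-up protocol are separate items, and one may properly be stricter than the other. But here the stricter one fails automatically on an event that the other is designed to tolerate.

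**Conclusion.** The point holds as an inconsistency between two progression criteria, of moderate importance. Taken as written, the forms criterion fails with the first woman lost to follow-up (at most 75% of her forms), while retention passes at 29/30 and down to 24/30.

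Three assumptions carry this:
- *For each participant* is read literally.
- The record check form, which the article calls by several names, is one form. If the names meant separate forms, a lost woman's share would be lower still.
- Exactly 30 women remain after withdrawals. The figure of six depends on this; the failure at one loss does not.

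Two stronger readings are tempting. One is that the protocol contains an arithmetic error, but it states no figure that is wrongly computed. The other is that the pilot will probably miss this criterion, but that depends on a loss rate that the documents do not give: across the assumed rates of 0.5% to 5%, the chance runs from 14% to 79%.

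**What to change.** Reword the data-collection criterion to: *at least 80% of participants have at least 80% of their data collection forms (7 of 8) complete*, and also report completion separately for each form. Six losses with all other women meeting the 7-form standard then give 24/30 = 80%, a pass, in line with the retention criterion. Seven give 23/30 = 76.7%, and both fail.

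Do not solve it by pooling to 80% of all expected forms (0.80 × 30 × 8 = 192 of 240). That rule would pass even if 24 of the 30 women lacked both follow-up forms: (6 × 8 + 24 × 6)/240 = 192/240 = 80%. The retention criterion already fails at seven losses, so the conflict would return in the opposite direction.

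The cost is one sentence and no extra data. The downside is a more lenient criterion, which tolerates incomplete records in up to 20% of participants (6 of 30). The per-form report keeps any concentration of gaps in one form visible.

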### Missing data and lost to follow-up {20C}

Every attempt will be made to collect full follow-up data for all study participants; it is thus anticipated that missing data will be minimal. The main analysis will use available data only; however, the amount of missing data will be assessed, and if necessary, sensitivity analyses will be undertaken. If the participant could not be contacted, but the patients’ medical records and notes were reviewed, the participant will be considered enrolled in the follow-up. The patient will be considered as lost to follow-up, if the participant could not be contacted and the patients’ file and notes were not reviewed.

### Data monitoring {21a}

The study may be monitored or audited in accordance with the current approved protocol, GCP, relevant regulations and standard operating procedures. This study does not include blinding and patients are following the standard clinical pathway where the only intervention is the taking of adipose tissue and plasma samples therefore a data monitoring committee is not required.

### Access to data {29}

All data will be collected only after the participant freely gave written consent to process their data in accordance with GDPR (this consent in included within the consent form for the study). Direct access to shared secure system will be granted to authorised representatives from the Sponsor and host institution for monitoring and/or audit of the study to ensure compliance with regulations.

### Harms {22}

The research protocol does not expose the participants to any risks as the study does not affect their clinical treatment. The collection of additional blood samples and adipose tissue samples during CS are the only additional study-specific procedures. These additional blood samples will be taken by a clinical member of the research team trained in phlebotomy. There is a consent request for these study-specific procedures to minimise the changes to routine clinical care and reduce the burden to participants. The risks associated with this research are minimal to participants.

All participants will be contacted at 30–40 days following CS to ask about post-surgical infections; this will not affect their clinical care in any way and does not pose any risks to participants.

### Provisions for post-trial care {30}

Participants within this trial will follow standard clinical procedures with the intervention being taking plasma and adipose tissues samples thus there is no specific post-trial care. As the participants are NHS patients, indemnity is provided through the NHS schemes. The University of Birmingham provides clinical research insurance for studies that it sponsors. This insurance is provided via membership of UMAL.

### Auditing {23}

The study may be monitored, or audited in accordance with the current approved protocol, GCP, relevant regulations and standard operating procedures.

### Protocol amendments {25}

The Investigator will submit and, where necessary, obtain approval from the Health Research Authority (HRA) and Health and Care Research Wales (HCRW) for all substantial amendments to the original approved documents.

## Discussion

### Interpatient pharmacokinetic variability of cefuroxime

Due to the great variability associated with pharmacokinetic measurements, the use of PBPK modelling is a common tool to understand the distribution of drugs. Specialist software packages are available that include details on pregnant population characteristics. SimCYP software will be used to model the blood and adipose concentrations of cefuroxime and to compare this modelled data to the experimental results from the C-LACE study. It is anticipated that this clinical data coupled with PBPK models will inform any future changes to doses of cefuroxime used for CS, particularly in relation to obese women.

### Definition of the end of study

The end of study is the date at which the follow-up interview is conducted at 30–40 days following CS. This is where the follow-up ends for all participants.

### Patient and public involvement

A similar study conducted by [name] and [name] (PREPS trial) involved the public and patients; those involved were supportive of any research undertaken to minimise the risks of post-surgical infections following CS [18]. Informal discussions about this study with women who have had CS have all been positive as the burden of participation is minimised where possible.

### Ethics and dissemination {31a-b-c}

Results of this trial will be submitted for publication in a peer-reviewed journal. The manuscript will be prepared by [name] and [name] with contributions from the local PI ([name]) and the local researcher ([name]) and authorship will be determined by mutual agreement. Authors must acknowledge that the trial was performed with the support of the Saudi Arabian Government. Currently, there are no plans for granting public access to the full protocol, participant-level dataset and statistical code.

### Provenance and peer review

The protocol has been peer-reviewed within the research team and by the research and governance team at the University of Birmingham as part of the agreement to sponsor the study and by the University of Birmingham’s Clinical Research Compliance Team (CRCT). Further, this protocol has been reviewed and approved by HRA and HCRW.

### Trial status

Ethical approval is granted (C-LACE protocol v0.4, 02 January 2020); the anticipated date of recruitment was 1st of September 2020; requirement expected to be completed on 1st of December 2020). This study was delayed due to COVID-19 epidemic.

## Data Availability

Direct access will be granted to authorised representatives from the sponsor and host institution for monitoring and/or audit of the study to ensure compliance with regulations. Access to the data retrieved from participants will be restricted. The clinical research team are those based at the hospital and the paperwork will not be transferred to the University of Birmingham. Following collection the data from all forms will be entered on a secure system at the NHS site (undertaken by the research midwife); this system can be accessed at the university and ensures anonymity for the participants. Researcher from the research team from the University of Birmingham will use the anonymous data to perform the data analysis.

## Abbreviations

BMI: Body mass index
CS: Caesarean section
GCP: Good clinical practice
IV: Intravenous
LC-MS/MS: Liquid chromatography with tandem mass spectrometry
MIC: Minimum inhibitory concentration
PBPK: Physiologically based pharmacokinetic
PIS: Participant information sheet
T>MIC: Time above the minimum inhibitory concentration
